### Sample size calculation

Given the novel and exploratory nature of the intervention for BCRL in this study, a minimum clinical sample size of 30 participants per group was selected (18),Assuming equal sample sizes for both groups and anticipating a 20% dropout rate, the total sample size was calculated as follows: N = 30o2×(1 + 20%)=72. Therefore, a total of 72 participants will be enrolled, with 36 participants in each group.(Reference: Whitehead AL, Julious SA, Cooper CL, Campbell MJ. Estimating the sample size for a pilot randomized trial to minimize the overall trial sample size for the external pilot and main trial for a continuous outcome variable. Statistical Methods in Medical Research. 2016;25 (3):1057-73).

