### Randomization and blinding

Eligible patients will be randomly assigned in a 1:1 ratio to receive either TEAS or Sham TEAS treatment. An independent staff member will assist in establishing and managing the randomization database. Patients in both the TEAS and Sham TEAS groups will be blinded to their group allocation. During each session, they will receive treatment in a closed unit. Except for the acupuncturists, all other researchers, including statisticians, outcome assessors, and data analysts, will be blinded to the group allocation. Furthermore, the acupuncturists will not be involved in outcome assessment or data analysis.

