The primary objective of this study is to determine the efficacy of TEAS for BCRL. In addition to recording subjective indices (e.g., VAS scores for perceived swelling and lymphedema-related symptoms) and objective clinical parameters (e.g., limb circumference changes and edema staging), this study highlights the crucial role of lymphatic system visualization and morphological monitoring in early diagnosis and assessment. Given that the initial pathological changes in lymphedema often manifest as slight thickening of the skin rather than an increase in subcutaneous tissue volume, this study incorporates ultrasound monitoring of skin thickness to provide early morphological evidence that is more sensitive than circumference measurements (23). Furthermore, to objectively assess the immediate impact of surgery on the lymphatic system, this study emphasizes the importance of preoperative baseline (T0) assessment. Serial near-infrared (NIR) fluorescence imaging, performed pre- and post-operatively (24), enables the dynamic observation of functional lymphatic vessel damage and the subsequent formation of collateral circulation. NIR possesses excellent tissue penetration, sensitivity, and high resolution, enabling non-invasive real-time tissue imaging. Indocyanine green (ICG) is a common NIR fluorescent dye used in BCRL assessment. Upon subcutaneous injection, ICG binds to plasma proteins in lymph, emitting detectable fluorescent signals that are transduced into lymphatic system images (25). The advantages of fluorescence imaging include the absence of ionizing radiation, minimal trauma, repeatability, real-time imaging, and ease of operation, making it suitable for preoperative assessment, intraoperative tracing, and postoperative follow-up. Furthermore, to comprehensively evaluate the intervention, this study will investigate the impact of TEAS on serum inflammatory factor levels. Finally, we will evaluate the statistical differences between TEAS and sham TEAS regarding BCRL incidence and quality of life.

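### Recruiting 72 does not keep the stated 30 per group after 20% dropout (28.8 remain), and the 30 is not derived from the incidence outcome on which efficacy is to be judged

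*Protocol article*

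**What the plan says.** All references are to the protocol article.

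- **Sample size calculation.** The section justifies its size by the new and exploratory character of the intervention, and on that ground "a minimum clinical sample size of 30 participants per group was selected". It then continues: "Assuming equal sample sizes for both groups and anticipating a 20% dropout rate, the total sample size was calculated as follows", and multiplies 60 by (1 + 20%) to reach 72. It concludes that "a total of 72 participants will be enrolled, with 36 participants in each group".
- **Source.** The reference printed at the end of that section is, by its title, about sizing a "pilot randomized trial to minimize the overall trial sample size for the external pilot and main trial for a continuous outcome variable". The section gives no event rate, effect size, significance level or power.
- **Primary outcome.** This is whether and when lymphedema occurs, up to the end of follow-up: one binary outcome and one time-to-event outcome.
- **Aim.** Study design says the trial is meant to evaluate efficacy and safety. The Discussion says: "The primary objective of this study is to determine the efficacy of TEAS for BCRL".
- **Analysis.** Data analysis sets a two-sided 5% level for all tests and imputes missing data by last observation carried forward. Removal criteria, by contrast, take out patients who are lost to follow-up or have incomplete data.

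**The concern.** There are two separate issues.

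1. **The inflation factor.** A dropout rate normally applies to the patients enrolled. To keep *n* after losing a fraction *d*, one enrols *n*/(1 − *d*), not *n*(1 + *d*). With the second form the trial misses its own minimum under its own assumption.
2. **The basis of the 30.** A number supported by a pilot-trial reference for a continuous outcome says nothing about what the trial can show for incidence. If the report then speaks of efficacy, readers may expect a precision that nobody calculated.

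At stake is mainly how the result can be read. The size is chosen on exploratory grounds, the stated aim is efficacy, and the protocol does not connect the two.

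**Working it through.** **Inputs.** From Sample size calculation: 30 per group, 20% dropout, 72 enrolled (36 per group). From Randomization and blinding: 1:1 allocation. From Data analysis: two-sided 5% level. Two background incidences appear in the article, neither used for the sample size: 58.3% after axillary dissection (Introduction) and about one-quarter of patients (Discussion).

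**Step 1: the plan's own figure.** 30 × 2 × (1 + 0.20) = 72. It reproduces exactly.

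**Step 2: what 20% dropout leaves.**
- Total: 72 × 0.8 = 57.6.
- Per group: 36 × 0.8 = 28.8, against a minimum of 30, so short by 1.2.
- Highest dropout that keeps 60 of 72: 1 − 60/72 = 16.7%, or 6 losses among 36.

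**Step 3: full inflation.**
- Total: 60/(1 − 0.20) = 75.
- Per group: 30/0.8 = 37.5, rounded up to 38, so 76 with equal arms.
- Check: 76 × 0.8 = 60.8.
- The gap from 72 is 3 to 4 patients in total.

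**Step 4: what the size means for incidence.** The article gives no effect size, so a halving of incidence is assumed here for illustration only. Normal-approximation power for two proportions, two-sided 5%:

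| Analysed per group | 58.3% vs 29.15% | 25% vs 12.5% |
|---|---|---|
| 29 | 61% | 23% |
| 30 | 63% | 23% |
| 36 (all randomised) | 71% | 27% |
| Needed for 80% power | 45 per group | 152 per group |

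The rows for 29 and 30 are almost the same. The limited power comes from the choice of 30, not from the dropout factor.

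**Step 5: expected precision.** The half-width of the 95% interval for the difference is 1.96 × √[(p₁(1 − p₁) + p₂(1 − p₂))/n]. At n = 29 per group:

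- Equal incidence, 25%: 1.96 × √(0.3750/29) = 22.3 points.
- Equal incidence, 58.3%: 1.96 × √(0.4862/29) = 25.4 points.
- Halved, 25% vs 12.5%: 1.96 × √(0.2969/29) = 19.8 points.
- Halved, 58.3% vs 29.15%: 1.96 × √(0.4496/29) = 24.4 points.

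That is about 22 to 25 points with equal incidence and about 20 to 24 points if incidence halves.

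**The case against.** **The shortfall hardly matters.** True. It is about one patient per group, and Step 4 shows that power at 29 and at 30 is nearly identical. A reader might infer that the inflation factor is what leaves the trial underpowered; the figures do not support that. If the 20% were meant as dropouts per completer (12/60), the factor would even be right, but the section speaks of a dropout rate and gives no such definition.

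**The section already says exploratory.** It does, and that partly explains a rule-of-thumb size. But the word is applied to the intervention rather than to the trial, and Study design and Discussion state an efficacy aim without that qualification. The fair charge is inconsistent labelling, not a missing admission.

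**The cited paper was not seen.** Correct. The section puts a numbered citation beside the 30 and prints a full reference at the end, and the article text at hand does not confirm that the two are the same. One may therefore not claim that the 30 comes from that paper's continuous-outcome rule. What stands is that the only title printed does not fit the primary outcome.

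**Dropouts may still be analysed.** Removal criteria exclude them, but Data analysis imputes missing values, and Data collection and management promises efforts to recover outcomes. The number analysed could lie anywhere between about 29 and 36 per group, so figures at 29 are one end of a range.

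**No misreading is planned.** A reader might infer that a non-significant result will be reported as no effect. The article only sets a general 5% level and nowhere says this. Dropping the test, or placing incidence above time of onset, would be a preference rather than a correction.

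**Conclusion.** The point holds in a limited form. Under the plan's own 20% dropout, 72 recruits leave 57.6 evaluable (28.8 per group), below its own minimum of 30; the minimum is kept only up to 16.7% dropout. This assumes that the rate applies to those enrolled and that dropouts do not count towards the minimum. Taken alone it is a minor wording error.

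More weight lies on the second part. The printed reference does not match an incidence and time-of-onset outcome, nothing in the section links 30 per group to an event rate or effect, and the exploratory rationale sits uneasily with the stated efficacy aim. These follow from the text alone. The power and precision figures are illustrations: they rest on the article's two background incidences, an assumed halving, and 29 to 36 analysed per group. The conclusion does not depend on them.

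**What to change.** Keep 72 and change the text:

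1. **Sample size calculation.** State that 72 will be randomised, that 20% dropout leaves about 57 to 58 evaluable (28 to 29 per group), and that 30 per group are kept only if dropout is 16.7% or less.
2. **Same section.** State that the size was not derived from the incidence outcome.
3. **Study design and Discussion.** Reconcile these with the sample size rationale by describing the trial as exploratory.
4. **Data analysis.** Report the between-group difference in 18-month incidence with its 95% confidence interval, alongside the planned test and the time-of-onset result.
5. **Expected precision, if quoted.** Give a range with its assumptions: at 29 per group, a half-width of about 22 to 25 points with equal incidence of 25% to 58.3%, or about 20 to 24 points if incidence halves.

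The cost is wording only, with no extra patients. The stated completer number becomes slightly less favourable and the efficacy claim more modest. Trial status reports 10 participants enrolled by July 2025 and follow-up is planned to run until June 2027, so the text can be corrected well before the 18-month results are in.

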### Randomization and blinding

Eligible patients will be randomly assigned in a 1:1 ratio to receive either TEAS or Sham TEAS treatment. An independent staff member will assist in establishing and managing the randomization database. Patients in both the TEAS and Sham TEAS groups will be blinded to their group allocation. During each session, they will receive treatment in a closed unit. Except for the acupuncturists, all other researchers, including statisticians, outcome assessors, and data analysts, will be blinded to the group allocation. Furthermore, the acupuncturists will not be involved in outcome assessment or data analysis.

### Intervention

Patients in both groups will receive basic treatment. Subsequently, they will undergo TEAS or Sham TEAS in separate treatment rooms to ensure no communication occurs between them. All participants will be informed that they may not perceive any sensation of stimulation during the procedure. All interventions will be administered by professional acupuncturists with at least 3 years of clinical experience who have completed standardized operational training. Both the observation and control groups will receive treatment once daily from the day before surgery until the third postoperative day (with treatment suspended on the day of surgery). Thereafter, treatments will be administered twice weekly for 4 weeks, totaling 12 intervention sessions.

### TEAS group

The treatment group will receive TEAS treatment.

Acupoint Selection: Tianfu (LU3), Taiyuan (LU9), Qingling (HT2), Shaohai (HT3), Xinshu (BL15), and Geshu (BL17) on the affected side. The localization of acupoints follows the Standard International Acupuncture Nomenclature proposed by the World Health Organization (WHO) (90/8579-Atar-8000) (19). Specific locations are listed in **Table 1**.

**Table 1 T1:** Specific locations of acupoints.

Acupoints	Location of acupoints
Tianfu(LU3)	In the anterior region of the arm, radial border of the biceps, 3 cun below the head of the anterior axillary stripe
Taiyuan(LU9)	In the anterior region of the wrist, on the radial side of the transverse stripe on the distal palmar side of the wrist, at the fluctuation of the radial artery
Qingling(HT2)	In the anterior region of the arm, 3 inches above the transverse line of the elbow, in the medial measuring groove of the biceps
Shaohai(HT3)	In the anterior region of the elbow, with the elbow flexed, at the midpoint of the line between the medial end of the transverse elbow stripe and the medial epicondyle of the humerus
Xinshu(BL15)	In the spinal region, below the spinous process of the 5th thoracic vertebra, 1.5 cun from the posterior median line
Geshu(BL17)	In the spinal region, below the spinous process of the 7th thoracic vertebra, 1.5 cun from the posterior median line

Body Position: Patients will be placed in the lateral decubitus position for all selected acupoints: LU3, LU9, HT2, HT3, BL15, and BL17.

Procedure: A KD-2A Transcutaneous Electrical Nerve Stimulation Therapeutic Apparatus (Beijing Yaoyang Kangda Medical Instrument Co. Ltd.) will be used. The skin around the acupoints will be disinfected. After the skin is dry, positive and negative electrode pads will be applied to the acupoints respectively. LU3 and LU9 will form one pair; HT2 and HT3 will form a second pair; and BL15 and BL17 will form a third pair.

Treatment Parameters: The frequency is set to 2/100 Hz (dense-disperse wave) with a pulse width of 50dt The output intensity will be gradually increased to the patient’s maximum tolerated level. The treatment duration is 30 minutes per session.

Treatment Course: Preventive intervention begins on the first day before surgery and continues daily until the third day after surgery. Subsequently, all patients will receive scheduled treatments twice a week (every Monday and Thursday at 10:00 AM) for 30 minutes per session. This phase consists of 8 consecutive scheduled sessions, extending to one month post-operation, for a total of 12 interventions.

### Sham TEAS group

The control group will receive Sham TEAS treatment. The acupoint selection, connection of electrode pads, retention time, and duration of the treatment course are identical to those of the treatment group. However, the stimulation intensity for the control group is first adjusted to the patient’s lowest sensory threshold and maintained for 30 seconds. Subsequently, the intensity is gradually decreased over the next 15 seconds until there is no current output. This brief period of stimulation ensures the maintenance of blinding. Similar to the treatment group, the device’s indicator light will flash, and the buzzer will sound.

### Basic treatment

All patients will receive standard preventive measures for lymphedema following axillary lymph node dissection for breast cancer, including preventive Intermittent Pneumatic Compression (IPC) therapy and preventive Manual Lymphatic Drainage (MLD). Patients will be instructed on how to perform limb rehabilitation exercises and advised to observe specific precautions for the affected upper limb postoperatively. These precautions include avoiding blood pressure measurements, blood draws, and injections on the affected side; preventing burns, cuts, infections, and insect bites on the affected limb; avoiding saunas or hot baths; avoiding strenuous repetitive movements with resistance using the affected limb; and avoiding excessive fatigue or maintaining a fixed posture for prolonged periods. Additionally, nutritional support will be strengthened.

### Follow-up

Since the onset of lymphedema typically occurs between 3 months and 3 years postoperatively, peaking at 18 months (5), the follow-up period is established as 1.5 years postoperatively. From the completion of the intervention until 1.5 years postoperatively, follow-up will be conducted once a month via telephone or WeChat. The content of these follow-ups includes the visual analogue scale (VAS) for perceived swelling and lymphedema-related symptoms. Additionally, an in-person appointment will be scheduled at 1.5 years postoperatively to collect data on upper limb circumference, edema stage, and severity.

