**Methods and analysis:**

A total of 72 breast cancer participants scheduled for axillary lymph node dissection will be recruited from Yunnan Provincial Hospital of Traditional Chinese Medicine and the First Affiliated Hospital of Kunming Medical University. They will randomly assigned in a 1:1 ratio to the TEAS group or the Sham TEAS group, with 36 cases in each group. Treatment will be administered once daily from the first day before surgery to the third day after surgery (paused on the surgery day), and subsequently twice a week for 4 consecutive weeks, totaling 12 intervention sessions. This will be followed by an 18-month follow-up period. The primary outcome measures are the incidence and time of onset of lymphedema within 18-month postoperatively. Secondary outcome measures include: VAS scores for perceived swelling and lymphedema-related symptoms evaluated at baseline (T0), from preoperative to postoperative day 3 (T1-T4), upon completion of twice-weekly post-discharge treatments (T5-T12), and during monthly follow-ups until 18 months postoperatively (T13-T29); changes in circumference, edema stage, and severity of the affected limb evaluated at T0, before and after treatments from preoperative to postoperative day 3 (T1a/b-T4a/b), before and after twice-weekly post-discharge treatments (T5a/b-T12a/b), and at T29; skin thickness ultrasound and lymphangiography of the affected limb performed at T0, T2, T12, and T29; and serum inflammatory factor levels measured at T0, T4, and T12. Adverse events occurring during the trial will be recorded.

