### Primary outcome

The incidence and time of onset of lymphedema from the postoperative period until the end of follow-up.

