Postoperative Day 2 (T3)											
Postoperative Day 3 (T4)											
Scheduled Treatment 1 (T5)											
Scheduled Treatment 2 (T6)											
Scheduled Treatment 3 (T7)											
Scheduled Treatment 4 (T8)											
Scheduled Treatment 5 (T9)											
Scheduled Treatment 6 (T10)											
Scheduled Treatment 7 (T11)											
Scheduled Treatment 8 (T12)											
Follow-up 1 (T13)											
Follow-up 2 (T14)											
Follow-up 3 (T15)											
Follow-up 4 (T16)											
Follow-up 5 (T17)											
Follow-up 6 (T18)											
Follow-up 7 (T19)											
Follow-up 8 (T20)											
Follow-up 9 (T21)											
Follow-up 10 (T22)											
Follow-up 11 (T23)											
Follow-up 12 (T24)											
Follow-up 13 (T25)											
Follow-up 14 (T26)											
Follow-up 15 (T27)											
Follow-up 16 (T28)											
Follow-up 17 (T29)											

Comparison of Limb Circumference Changes, Edema Staging, and Severity: Changes in the circumference, edema stage, and severity of the affected limb will be observed at baseline (T0), before and after treatments from preoperative to postoperative day 3 (T1a/b-T4a/b), before and after twice-weekly post-discharge treatments (T5a/b-T12a/b), and at 18 months postoperatively (T29). The mean values and differences in circumference before and after treatment will be compared between the two groups to evaluate the effect of treatment on limb edema. Staging and measurement standards are detailed in **Table 4**.

**Table 4 T4:** Data collection form for upper limb circumference, edema staging, and severity.

Name: Age: Operated limb: Date of surgery:													
Upper limb circumference measurement							Edema stage				Edema severity		
Measurement timepoint	Measured limb	Palmar crease	Wrist crease	10 cm above wrist crease	Elbow crease	5 cm above elbow crease	Stage 0	Stage I	Stage II	Stage III	Mild	Moderate	Severe
Preoperative (T1)	L												
	R												
Postoperative Day 1 Pre-treatment T2a	L												
	R												
Postoperative Day 1 Post-treatment T2b	L												
	R												
Postoperative Day 2 Pre-treatment T3a	L												
	R												
Postoperative Day 2 Post-treatment T3b	L												
	R												
Postoperative Day 3 Pre-treatment T4a	L												
	R												
Postoperative Day 3 Post-treatment T4b	L												
	R												
Scheduled Treatment 1 Pre-treatment T5a	L												
	R												
Scheduled Treatment 1 Post-treatment T5b	L												
	R												

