### Data analysis

Software and Data Handling: All statistical analyses will be performed by an independent statistician using SPSS 25.0 software (IBM, Armonk, NY). Missing data will be imputed using the Last Observation Carried Forward (LOCF) method.

Normality and Continuous Variables: Measurement data will be assessed for normality using the Shapiro-Wilk (S-K) test. Data conforming to a normal distribution will be expressed as mean ± standard deviation (SD). Intra-group comparisons (pre- and post-treatment) will be analyzed using the paired samples t-test, while inter-group comparisons will be performed using the independent samples t-test. Measurement data that does not follow a normal distribution will be analyzed using non-parametric rank-sum tests.

Categorical Variables and Significance: Enumeration data (categorical data) will be presented as percentages or constituent ratios, and differences between groups will be analyzed using the Chi-square (χ²) test. All statistical tests will be two-sided, with the significance level set at αt 0.05. A P-value < 0.05 will be considered statistically significant.

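### Time of onset is a co-primary outcome, but the arm is not measured between about month 1 and month 18, so measured onset in that period cannot be dated and adds almost nothing to 18-month incidence

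*Protocol article*

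**What the plan says.** The abstract states: "The primary outcome measures are the incidence and time of onset of lymphedema within 18-month postoperatively". The Primary outcome section repeats the pair: "The incidence and time of onset of lymphedema from the postoperative period until the end of follow-up".

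For circumference, stage and severity, the Secondary outcomes section lists baseline, the inpatient treatment days, then "before and after twice-weekly post-discharge treatments (T5a/b-T12a/b), and at 18 months postoperatively (T29". Nothing is listed between T12 and T29. The treatment course under TEAS group places T12 in calendar time: "This phase consists of 8 consecutive scheduled sessions, extending to one month post-operation, for a total of 12 interventions". Skin ultrasound and lymphangiography (T0, T2, T12, T29) leave the same gap.

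Between those points the Follow-up section provides remote contact: "From the completion of the intervention until 1.5 years postoperatively, follow-up will be conducted once a month via telephone or WeChat". On what is collected: "The content of these follow-ups includes the visual analogue scale (VAS) for perceived swelling and lymphedema-related symptoms". The return to direct assessment is a single visit: "an in-person appointment will be scheduled at 1.5 years postoperatively to collect data on upper limb circumference, edema stage, and severity". The same section says that onset usually begins from 3 months after surgery and peaks at 18 months.

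For between-group comparison of measurement data, the Data analysis section says "inter-group comparisons will be performed using the independent samples t-test", with a rank-sum test if the data are not normal and a chi-square test for categorical data. No method for censored times is listed, and no test is assigned to time of onset by name.

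**The concern.** A date of onset can be no finer than the interval between the last assessment without lymphedema and the first with it. Here that interval runs from about month 1 to month 18 for nearly every expected case. Stage rests on clinical signs and severity on the difference in circumference between the arms, and neither is listed for a telephone contact. Half of the primary outcome would then either repeat the 18-month yes/no result or rest on unmeasured symptom reports that the protocol treats as secondary.

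The analysis adds a second difficulty. Participants who stay free of lymphedema are the successes of a prevention trial, and they have no onset time. A t-test or rank-sum test on recorded onset times leaves them out unless a rule says otherwise. What remains is a comparison among cases, a subset formed after randomisation, and it hardly responds to prevention.

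**Working it through.** **The plan's own figure.** The sample size section gives 30 × 2 × (1 + 0.20) = 72, which reproduces. It contains no assumption about incidence, hazard ratio or onset time. I use 30 completers per arm below.

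**Length of the gap.** T12 is at about month 1 and T29 at month 18: 18 − 1 = 17 months, and 17/18 = 94% of follow-up. The protocol's typical window starts at month 3, so every typical onset before T29 falls inside the gap.

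**Share of onsets in the gap under a constant hazard.** With 18-month incidence p, F(t) = 1 − (1 − p)^(t/18), and the share is 1 − F(1)/p. The document gives two incidence figures: 58.3% after axillary dissection (Introduction) and about one-quarter (Discussion).
- p = 0.583: F(1) = 0.047, share = 1 − 0.047/0.583 = 92%.
- p = 0.25: F(1) = 0.016, share = 1 − 0.016/0.25 = 94%.

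If these onsets are dated at the visit that finds them, they all equal 18 months and carry no timing information.

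**Participants without an onset time.** Of 30 control completers: 30 × (1 − 0.583) = 12.5 at the high figure and 30 × (1 − 0.25) = 22.5 at the low one.

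**Why a cases-only comparison is insensitive.** Under exponential onset with hazard λ, mean onset among cases is 1/λ − 18·S/(1 − S), where S is the 18-month onset-free proportion. At 58.3% control incidence:
- Control: λ = −ln(0.417)/18 = 0.0486, so 20.6 − 18 × 0.417/0.583 = 7.7 months.
- TEAS at hazard ratio 0.5: S = 0.417^0.5 = 0.646, so 41.2 − 18 × 0.646/0.354 = 8.3 months.

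Halving the hazard lowers incidence from 58.3% to 35.4% but moves mean onset among cases by only about 0.6 months.

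**Simulated rejection rates** (3,000 to 4,000 trials, 30 per arm, two-sided 0.05, exponential onset). The hazard ratios are assumptions, since the document gives none. The log-rank column supposes exact or monthly onset dates, which the visit schedule does not supply.

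| Control incidence | Hazard ratio | t-test, cases only | Rank-sum, cases only | Log-rank, dated onsets | Chi-square, 18-month incidence |
|---|---|---|---|---|---|
| 58.3% | 0.5 | 7% | 6% | 44% | 43% |
| 58.3% | 0.35 | 7% | 6% | 73% | 72% |
| 25% | 0.5 | 5% | 3% | 21% | 20% |
| 25% | 0.35 | 4% | 2% | 36% | 36% |

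At 25% incidence some trials have fewer than two cases in an arm. The cases-only test then cannot be run, and those trials count as non-rejections.

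**The alternative of keeping everyone.** A rank-sum test on all participants, with onset-free ones tied at 18 months, rejects in 42% at hazard ratio 0.5 and 71% at 0.35 (58.3% incidence), with 5–6% under no effect. That is close to log-rank, but it also presupposes dated onsets.

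**The case against.** Three points can be made for the protocol.

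First, the monthly scores could date a symptomatic onset to within a month, and the Primary outcome section does not say that onset is defined by circumference. The inclusion criteria refer to diagnostic criteria that are not in the text shown, so the definition cannot be checked here. A reader might infer that onset cannot be observed at all, but the document does not support that. What stands is narrower: measured or staged onset cannot be dated inside the gap, and no shown rule links the symptom scores to the primary outcome.

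Second, no test is assigned to time of onset, and an analysis plan that is not shown may supply one. A reader might infer that the outcome cannot be validly tested. That goes too far, because a listed rank-sum test applied to all participants would be valid under complete follow-up to a common cut-off, and nearly as powerful as log-rank. The 2–7% figures apply only if the comparison is restricted to cases, which the protocol neither states nor rules out. An analysis plan can add a method or a ranking rule, but it cannot recover arm measurements that were never scheduled.

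Third, a reader might infer that two primary outcomes each tested at 0.05 come close to doubling the false-positive risk. The document states no success rule for the pair, and the two outcomes share the same events. When both were tested on all participants, the simulated risk was 5–8%. The present point does not rest on multiplicity.

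**Conclusion.** The point stands in this form. The protocol fixes a co-primary outcome that its own visit schedule cannot date. For about 17 of 18 months the arm is not assessed, and 92–94% of onsets under a constant hazard, or all typical ones under the protocol's stated window, fall there. As measured, time of onset adds almost no information beyond 18-month incidence. Incidence itself remains observable at T29 and testable by chi-square, so the trial keeps a usable primary outcome.

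The schedule finding rests on the text alone. The rejection rates depend on assumed hazard ratios, 30 completers per arm and exponential onset. The last is a simplification, since the protocol expects onset from month 3 with a peak at month 18. A better test for onset is also no remedy for low power: at 25% control incidence log-rank with dated onsets reaches only 21% at hazard ratio 0.5.

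**What to change.** - **Primary:** name one primary outcome, lymphedema at the 18-month in-person measurement or at an earlier in-person measurement. Test it once at two-sided 0.05 and report a risk difference with 95% CI.
- **Onset:** move it to secondary. Keep all randomised participants and censor those without onset. Then choose one of two definitions in advance. Either treat onset as interval-censored between the last negative and first positive arm measurement, or label it as patient-reported symptom onset under a prespecified score rule and use Kaplan-Meier and log-rank.
- **Limitation:** state that edema arising and resolving between months 1 and 18 is not captured.

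The interval-censored option is honest but will show little, because nearly all onsets share one interval. If the sponsor wants measured onset to stay primary, interim or symptom-triggered arm measurements would be needed, and these take extra resources.

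The main change needs no new visits. It costs a protocol and registry amendment, reported to the ethics committee, and one headline outcome becomes secondary. The Trial status section gives 10 participants enrolled as of July 2025, so at that stage most follow-up still lay ahead.
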